#### Criteria for discontinuing or modifying allocated interventions

No criteria will be determined for discontinuing or modifying the allocation order. Participants who do not comply with the interventions will also be evaluated and will provide information about when they abandoned the intervention for later accounting. All of them will have their variables analyzed by intention to treat.

#### Strategies to improve adherence to interventions

A trained researcher will be responsible for supporting participants who may find it challenging to adhere to the study interventions. Before obtaining consent from participants to participate in the research, we will provide information about the research and its relevance to their health during the experimental procedures. In addition, the research team will be trained to be available to resolve doubts. At the end of the study, the participants will be invited to participate in a physical training and nutrition group for the elderly at the Escola de Educação Física e Esporte de Ribeirão Preto, USP, Brazil.

#### Relevant concomitant care is permitted or prohibited during the trial

Prior to carrying out the stages of the experimental procedures, the participants will receive instructions and guidelines to fill in a food diary on the days prior to measuring the variables of each intervention protocol, the foods, and amounts ingested from breakfast (first meal) until supper (last meal). We will ask the participants to eat the same foods and in similar amounts on the day before each collection. According to the study by Griesenbeck et al. [36], a list of foods that are considered high in nitrate and participants will be instructed not to ingest during the study. The amount of carbohydrate, protein, fat, and nitrate intake will be assessed by a trained nutritionist through a specific software (Nutritionist Pro® v. 7.3, Axxya Systems, Woodinville, WO, USA). Potential drug-food interactions are possible, but it is difficult to tease these out in our study; however, participants’ food consumption and drug regimen will be well characterized, and our cross-over design will minimize the impact of such potential interactions on intraindividual responses, as the each participant will undergo all different conditions (placebo and experimental). On the days of the laboratory visit, not having breakfast as a standard meal will be provided 40 g of whey protein (Top Whey 3w, Max Titanium®, SP, Brazil) before executing the experimental protocols. Avoid performing vigorous physical efforts the day before and on each experiment; we will ask participants not to change your physical activity habits while participating in the study. Do not drink caffeine-based beverages and other stimulants or alcoholic beverages within 12 h and 24 h, respectively, prior to each stage of the study, and do not use mouthwash during all experimental protocols and between them in order to avoid the reduction of the oral microbiota responsible for nitrate metabolism [37].

#### Initial evaluations

Participants will be identified by collecting the following information: age (years), body mass (kg), height (cm), body mass index (BMI), hip circumference (HC), waist circumference (WC), and circumference calf (CP). Anthropometric measurements will be obtained according to the recommendations described by Lohman et al. [38]. BMI will be calculated using the following formula: body mass (kg)/height^2^ (m). The waist/height ratio will be calculated by dividing the waist circumference by the height obtained in centimeters. The following assessments will also be carried out:Body composition: The fat percentage of the participants will be collected for a better characterization of the studied sample. The dual X-ray absorptiometry (DXA) will analyze the body composition, as lean body mass and fat mass. The exam will be conducted by a clinician trained in radiology at the Laboratory of Cineantropometry and Human Development [39].Familiarization of participants for the VO2peak test: A familiarization protocol will be used to improve the reliability of the data obtained with the VO2peak test. The participants will be physically inactive and will not be acclimated to the physical exercise, which may underestimate the values obtained in the test. At this stage, as a way of monitoring and safety of the participants, three collections of systolic and diastolic blood pressure will be performed before any procedure. On the first day, we will collect blood (15 mL) to analyze the blood glucose and lipid profile. We will use these data to characterize the sample. Prior to the VO2peak determination test, the participants will undergo a familiarization phase with the treadmill during three sessions performed on three different days. The Bruce protocol will be applied to determine the VO2peak. The values obtained during this phase will not be considered in the study [40].Determination of VO2peak (maximum exertion test): Another day will be scheduled to perform the VO2peak test of the participants so that the participants come to the laboratory in the fed state and with light clothes. The test will be performed on a treadmill (TPEE; Inbrasport ATL 2000®) using the Bruce protocol for the consequent use of 65–70% of the speed corresponding to the VO2peak for the load applied in the following steps. For VO2peak analysis, expired gases are analyzed in a commercial Teem 100 - VO 2000 system (Aerosport, Ann Arbor®, USA) previously validated by Novitsky et al. [41] and Wideman et al. [42] and periodically calibrated with volumes and gases of known concentration.

#### Exercise variables

On the first day, the collections will occur after the participants ingested 140 mL of beet juice (with or without nitrate). The seventh day of beet juice ingestion (70 mL) (with or without nitrate) will also be collected. On the collection days (first and seventh days of intervention), the variables will be obtained at the following times (Fig. 1):

I)Rest phase (zero to 135th min): After drinking the juice, the participants will remain at an initial rest in a sitting position. Then, 30 min before starting the measurements, the participants will be instructed to empty their bladders. Upon returning to the room, a recording strap (Polar® H10) will be placed on the chest, in the region of the distal third of the sternum, to record beat-to-beat HR throughout the collection, mediated by a heart rate monitor (Polar® RS800CX, Finland). Then, the participants will be placed on a stretcher in the supine position and will remain at rest. After the remaining time, HR values will be recorded (120th minute), HRV recording (120th to 125th min), systolic blood pressure (SBP) (125th minute), diastolic blood pressure (DBP) (125th minute), blood collection (15mL) (125th min), and analysis of endothelial function (flow-mediated dilation) (125th to 135th min).II)Physical exercise (135th to 175th min): Participants will perform the physical exercise for 40 min on a treadmill at a speed corresponding to 65–70% of VO2peak [29]. In this phase, the highest HR value reached during the exercise will be recorded, and the HRV recording will also be carried out in the last 5 min (35th–40th min).III)Recovery phase (175th to 235th min): At the end of the activity, the participants will be placed in the supine position again and will be monitored for another 60 min, recording their HR at 30 s, 60 s, 120 s, 180 s, and 300 s. Blood collection (15 mL) will be performed between 5 and 10 min after exercise. HRV will be recorded after exercise at the following times: 0–5 min, 10–15 min, 20–25 min, 30–35 min, and 40–45 min. SBP and DBP will be recorded after exercise at the 45th minute and 60th minute post-exercise. To avoid errors in the measurements of the evaluated parameters, a single evaluator will perform these measurements throughout the experiment. The flow-mediated dilation technique to assess endothelial function will be employed after exercise during the 50th–60th minute post-exercise interval.

**Fig. 1 Fig1:**
[figure not shown]
Experimental procedures of the study and collecting data

### Primary outcomes

#### Blood pressure

The measurement of systolic and diastolic blood pressure will be performed indirectly using a digital sphygmomanometer (OMRON M2, Model HEM-7121-E, Jundiaí, São Paulo, Brazil) previously calibrated on the participants’ left arm.

### Secondary outcomes

#### Heart rate variability analysis

For the analysis of HRV indices, heart rate will be recorded beat by beat throughout the experimental protocol with a sampling rate of 1000 Hz. Stable series with sections of 256 RR intervals will be selected. The last 256 R-R intervals of each 5-min recording window will be analyzed [43]. In these series, digital and manual filtering will be performed to eliminate premature ectopic beats and artifacts. Only those with more than 95% of sinus beats will be included [44].

#### Linear indices

The time-domain analysis will be performed using the standard deviation of the mean of normal R-R intervals (SDNN) and square root of the mean of the square of differences between adjacent normal R-R intervals (RMSSD) indices. For the analysis of linear indices in frequency and time domains, the program Kubios HRV 2.1 analysis® will be used [45]. High-frequency spectral components (HF: 0.15–0.40 Hz) in absolute units (ms^2^) will be used to analyze HRV in the frequency domain. We will choose not to evaluate the low-frequency index (LF: 0.04–0.15 Hz) and the LF/HF ratio since the scientific literature demonstrates that its concept is defective and lacks empirical support to characterize vagal balance—sympathetic [46]. The spectral analysis will be calculated using the fast Fourier transform.

#### Ultra-short-term analysis

Ultra-short-term analyses will be performed with the RMSSD index. For a more detailed analysis of the reactivation of parasympathetic flow after exercise, the last 60 intervals of the resting recording will be selected for comparison with the first 5 min post-exercise divided into 60 cardiac intervals.

#### Heart rate recovery analysis

Heart rate (HR) will be recorded continuously at rest (HR rest), during exercise, and recovery. Resting HR will be measured immediately before the test, with the participants still standing on the treadmill. Reserve HR will be calculated as the difference between peak HR during exercise and at rest. The chronotropic response (CR%) will be calculated using the following formula: ([HRpeak − HRrest/220 – age − HRrest] × 100). HR recovery (HRrec) will be calculated as the difference in HR after the 30 s, 60 s, 120 s, and 180 s of recovery concerning HRpeak during exercise (HRrec30s, HRrec60s, HRrec120s, and HRrec180s, respectively). A reduced HRrec after exercise will be established when differences ≤ 12 bpm are found in HRrec60s [27].

#### Endothelial function

The flow-mediated dilatation (FWD) technique will be performed with a bidirectional ultrasound device (2D), with color and spectral Doppler and linear probe transducer with a frequency of 14 Mhz from the Toshiba® brand. The technique of Celemajer et al. [47]. First, the participant will be positioned in dorsal decubitus (supine position) with controlled abduction of the right arm. The linear transducer will be positioned in the medial phase of the arm to obtain a longitudinal image of the right brachial artery in B-mode (parallel to the transducer), 5–10 cm to superior the antecubital crease.

After measuring the basal diameter (D1), the transducer location will be marked with an anthropometric evaluation marker (Penta Texta 700 Fine) so that the post-occlusion diameter measurement can be performed at the same location. Subsequently, the brachial artery will be occluded for 5 min, with a pressure cuff placed on the arm with a pressure adjustment slightly higher than the SBP. After 60 s of cessation of inflation, the artery’s post-occlusion diameter (D2) will be measured. The measurements of D1 and D2 will be carried out in the same place in the vessel. The DILA will be calculated by the formula (DILA (%) = D2 − D1/D1 × 100).

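### Flow-mediated dilation rests on a loosely set cuff, one diameter reading at 60 s and a percentage of a post-juice baseline, so DILA% alone may blur or misstate the vascular effect

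*Protocol article*

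**What the plan says.** All references are to the protocol article.

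- **Artery and arm.** Under Endothelial function the probe is placed "to obtain a longitudinal image of the right brachial artery in B-mode". Under Blood pressure the device is "previously calibrated on the participants’ left arm". No right-arm systolic reading is described.
- **Cuff.** Endothelial function sets the occlusion time at 5 min. The inflation rule reads: "with a pressure cuff placed on the arm with a pressure adjustment slightly higher than the SBP". No number is attached to the margin. The ultrasound device has colour and spectral Doppler, but the text does not say that absence of flow is checked.
- **Timing of D2.** "After 60 s of cessation of inflation, the artery’s post-occlusion diameter (D2) will be measured". No other diameter after cuff release is mentioned.
- **Outcome.** "DILA (%) = D2 − D1/D1 × 100". The brackets are missing as printed; (D2 − D1)/D1 × 100 is evidently meant.
- **When D1 is taken.** Under Exercise variables the resting measurement falls at 125 to 135 min after the juice. The second "will be employed after exercise during the 50th–60th minute post-exercise interval", so it also follows the juice. The text schedules no diameter before ingestion.
- **Mechanism.** Background and rationale gives nitric oxide derived from nitrate a central part in vasodilation.

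**The concern.** Endothelial function is named in the objectives and bears on the nitric oxide hypothesis. Three stated rules affect whether DILA% measures it cleanly.

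1. A cuff only a little above a pressure measured in the other arm may not fully stop flow if the right-arm pressure is somewhat higher, or if it rises during the 5 min. The stimulus would then vary between measurements.
2. One reading at 60 s captures the peak only if the peak falls there. Otherwise the response is understated and, if the time of peak differs between treatments, a change in timing is read as a change in size.
3. On the trial's own mechanism, nitrate may already have widened D1. A percentage taken from a post-treatment baseline cannot by itself distinguish less dilation from an artery that was wider to begin with.

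At stake is the reading of this secondary outcome: a null or lower DILA% under nitrate could be misread as absent or impaired vascular benefit.

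**Working it through.** The plan states no expected value, SD or sample size for flow-mediated dilation, so there is no figure of its own to reproduce here. Its minimum of 11 participants rests on blood pressure (5 mmHg, variation 4 mmHg, two-sided 5%, 80% power): 2 × (1.960 + 0.842)² × (4/5)² = 10.05, rounded up to 11. Nothing below touches it.

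The diameters, inter-arm SDs and capture fractions below are **assumptions**; the document gives none of them.

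**1. Baseline.** DILA = (D2 − D1)/D1 × 100 = (D2/D1 − 1) × 100. It falls whenever D1 widens by a larger percentage than D2. Assume placebo D1 = 4.00 mm and D2 = 4.20 mm, so DILA = 0.20/4.00 = 5.0%.

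| Under nitrate | DILA |
|---|---|
| D1 +2% (4.08), D2 +1% (4.242) | 0.162/4.08 = 3.97% |
| D2 unchanged, D1 +1% | 0.16/4.04 = 3.96% |
| D2 unchanged, D1 +2% | 0.12/4.08 = 2.94% |
| D2 − D1 unchanged (0.20 mm), D1 +1% to +5% | 4.95% to 4.76% |
| D2 − D1 up 10% (0.22 mm), D1 +1% to +5% | 5.45% to 5.24% |

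In the first row both diameters are larger, yet DILA drops by about one percentage point. The last two rows set the limit. Division by a wider D1 costs little by itself. A material fall needs baseline widening that uses up part of the absolute dilation.

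**2. Cuff.** Let the right-minus-left systolic difference, including device error, be normal with mean 0 and SD s, and let the cuff be set m above the left-arm value. The chance that right-arm pressure exceeds the cuff is 1 − Φ(m/s).

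| Margin m | s = 4 mmHg | s = 10 mmHg |
|---|---|---|
| 5 mmHg | 11% | 31% |
| 10 mmHg | 1% | 16% |
| 20 mmHg | 0% | 2% |

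The unquantified margin therefore largely decides whether occlusion is complete. In a crossover, a stable inter-arm difference acts on both treatments alike, so the main result is noise and attenuation.

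**3. Reading at 60 s.** Assume true peaks of 5% on placebo and 6% on nitrate, a gain of 1.0 point.

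- Same fraction of the peak captured in both conditions, 70% to 90%: the gain becomes 0.7 to 0.9.
- 90% captured on placebo and 75% on nitrate: 4.5 − 4.5 = 0.
- 90% and 70%: 4.2 − 4.5 = −0.3.

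Loss or reversal therefore requires the juice to change the time course. A fixed reading time with a common time course only attenuates.

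**The case against.** The strongest reply is that the text already specifies occlusion as the state to be reached, with Doppler on the device, and that operator detail may sit in a full protocol or in the cited technique. It never says that the left-arm value sets the right-arm cuff. That is an inference from the only arm described. This stands as a caution, but the cuff wording, the 60-s reading and the formula are stated rules, and they would govern as written.

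A reader might go further and infer that the method is biased against nitrate. The document does not support that. A cuff that follows systolic pressure keeps its margin roughly constant, and within-woman comparison removes much of a constant arm difference. Nothing in the text shows that juice shifts the time of peak, and exercise is done under both treatments. Nor does it give evidence that nitrate widens D1 by more than D2.

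A reader might also infer that a set share of the treatment effect is lost. A fall such as 5.0% to 4.0% is a change in one DILA value under assumed diameters, not a fraction of an estimated treatment difference.

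Finally, the protocol relies on plasma nitrite to attribute effects to nitrate intake, and flow-mediated dilation is one of many secondary outcomes. Both are true, and both limit the weight of the point.

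**Conclusion.** The point holds in limited form. Three measurement rules are fixed in a way that makes DILA% less precise and, taken alone, hard to interpret: an unquantified cuff margin tied to a systolic pressure described only in the other arm, a single 60-s diameter, and a percentage of a post-juice baseline. The expected consequence of the first two is noise and attenuation. A null or reversed DILA% despite a wider artery is arithmetically possible. It requires either baseline widening that consumes dilation (for example 5.0% to 3.97%) or a treatment-dependent time of peak. Both rest on assumed values, and neither is shown to occur. The trial's conclusions on blood pressure do not depend on this.

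**What to change.** - **Cuff.** State one rule, the same for every session, with a clear margin above systolic pressure measured in the occluded arm, and confirm absent flow with the Doppler already in use. An entry limit on systolic pressure is not a safe anchor for this rule: Eligibility criteria joins the systolic range to a diastolic range by an or, and it describes entry, not later sessions.
- **D2.** Record diameter from cuff release through about 120 s and take the peak as D2. Keep the 60-s value as a secondary reading.
- **Reporting.** Give D1, D2 and D2 − D1 by treatment beside DILA%, and compare D1 between treatments. Print the formula with its brackets.
- **Model.** A D1-adjusted analysis of D2 may be added only as a sensitivity analysis. D1 is itself post-treatment, so adjusting for it can remove part of the effect of interest.

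Cost: a right-arm pressure reading, a longer image file to read and slightly more cuff discomfort. The 10-min slot becomes tight: about 2 min of baseline, 5 min of occlusion and 2 min of recording make 9 min, and the resting slot opens at the same minute as the pressure readings and blood draw. Trial status puts the end of recruitment at about 31 January 2023. For sessions already completed, the acquisition changes apply only if the recordings were stored, but the reporting changes still can be made.

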#### Blood tests

##### Quantification of plasma concentrations of nitrite

Plasma concentrations of nitrite will be used to indirectly quantify the changes in nitric oxide (NO) concentration. This analysis will be necessary before and after exercise to attest that the possible effects found will be due to increased nitrate intake, which was later converted into nitrite. The Nitric Oxide Analyzer Sievers device (NOATM) – model 280i, USA, will be used. In the sealed glass chamber of the device, 300 μL of blood samples will be injected in contact with 8 mL of acidified triiodide solution (2 g of potassium iodide and 1.3 g of iodine dissolved in 40 mL of water with 140 mL of acid acetic). NO will be produced in the form of gas by the reaction of nitrite with the iodide solution. A continuous flow of nitrogen gas carries NO to the other chamber for reaction with ozone—the detection of NO in the device is based on the gas-phase reaction of NO with ozone [48].

##### Quantification of plasma lipid peroxidation by MDA

Oxidative stress will be estimated through the secondary products of lipid peroxidation and will be analyzed through the quantification of Malondialdehyde (MDA). MDA is considered a reliable general biomarker of plasma oxidative damage. The quantification of MDA will be performed using high-performance liquid chromatography (HPLC), with visible detection (VIS), according to the methodology of Grotto et al. [49]. After the centrifugation step, the plasma will be separated. In the volume of 75 μL of plasma, 25 μL of water and 25μL of NaOH3N will be added, which will be incubated for 30 min in a horizontal agitation system with heating at 60 °C. Afterward, 125 μL of 6% H3PO4 and 125 μL of 0.8% TBA will be added to the samples, and the product will be incubated for 45 min at 90 °C. Then, 50 μL of 10% sodium dodecyl sulfate (SDS) will be added to the samples. The samples will be extracted with 300 μL of n-butanol after 1 min of vortexing and will be centrifuged at 3000*g* for 10 min; 20 μL aliquots of the organic phase will be injected into the chromatograph [49].

##### Quantification of plasma non-enzymatic antioxidant defenses by FRAP

This quantification will be done by the ferric reducing ability of plasma (FRAP) technique, whose principle is based on reducing the ferric ion Fe3+ to ferrous Fe2+. For this, three solutions will be prepared: A (acetate buffer: 300 mM, pH 3.6, and 40 mM HCl), B (TPTZ (2,4,6-tri[2-pyridyl]-s-triazine), 10 Mm), and C (ferric chloride hexahydrate (FeCl3.6H2O), 20 mM), forming the working reagent A + B + C in the proportion 10:1:1 (V/V). Then, 80 μL of the plasma obtained will be added to a mixture of deionized water (250 μL) with the working reagent (2.4 mL). This solution containing the sample will be incubated in a water bath at 37 °C for 15 min in the dark. Then, the FRAP concentrations will be estimated by interpolating the absorbances determined in the samples with those determined in a standard curve, which will be prepared by diluting a standard solution of ferrous sulfate (Fe11) in distilled water, obtaining final concentrations of 0, 31.25, 62.5, 125, 250, 500, and 1000 μmol/L. Afterward, this solution will be placed in a microplate. The absorbances (at 593 nm) will be read in parallel with a standard curve of ferrous sulfate using a microplate reader spectrophotometer [50].

##### Hormones, catecholamines, inflammatory, and mitochondrial markers

We will evaluate the concentrations of molecules directly and indirectly associated with the cardiovascular system before and after using beet juice rich in nitrate. These analyses allowed us to verify the influences and the relationships that inflammation markers, hormones, and catecholamines have with the cardiovascular system on the effects of beet juice rich in nitrate. Plasma concentrations of leptin, ghrelin, adiponectin, lipoprotein lipase, and hormone-sensitive lipase will be determined from a quantitative enzymatic assay using specific commercial kits (Linco Research Inc., St. Louis, MO, USA). The analysis will be carried out to evaluate concentrations of the interleukins (IL-6 and IL-10), tumor necrosis factor-alpha (TNF-α), interferon-y (IFN-y), C-reactive protein (CRP), nuclear factor-kappa B (NF-kB), vascular endothelial growth factor (VEGF), monocyte chemotactic protein 1 (MCP-I), vascular cell adhesion molecule 1 (VCAM-I), intercellular cell adhesion molecule-1 (ICAM-I), and N-terminal portion of the pro-hormone natriuretic peptide (NT-proBNP) (Biolegend, San Diego, CA, USA). Plasma catecholamines (epinephrine and norepinephrine) will be tested using a commercially available dual-purpose enzyme-linked immunosorbent assay (ELISA) kit (ABNOVA, Taiwan) [51]. Mitochondrial biogenesis will be evaluated by quantifying factor-1 and factor-2 markers related to NF-E2 (NRF1 and NRF2) by peroxisome proliferator-activated receptor gamma coactivator 1-alpha (PGC-1α), using an ELISA kit specific (ABCAM, USA) [52].

